The first trial tested the safety and immunogenicity of the mixture of three antigens given at a single site or given separately at three sites. For the first vaccination, volunteers received 3 x 100 g of antigen or 3 x 50 g; all received 3 x 20 g in the second vaccination. In the second trial, which compared the safety and immunogenicity of different doses of a mixture of the three antigens, the subjects received 3 x 50 g, 3 x 13 g or 3 x 4 g for the first vaccination and 3 x 20 g, 3 x 13 g or 3 x 4 g for the second vaccination, respectively. No serious adverse events were reported in either trial but local reactions, particularly pain and tenderness, occurred in the majority of subjects, These reactions lasted for up to a few days and were also seen in subjects receiving the adjuvant alone. One subject had a local reaction that was severe for three days before resolving gradually over three weeks.

In both trials some subjects had delayed local reactions with pain, tenderness and/or swelling developing 10 days or later after vaccination. These reactions were clearly related to antigen dose with the majority occurring in subjects receiving the mixture of 3 x 100 g antigen in a single site and none occurring in subjects receiving the lowest antigen dose or the adjuvant alone. The delayed reactions were mild to moderate in all but two subjects. One developed severe pain and swelling in the injected thigh 10 days after the vaccination, which resolved over a week. This subject was given 20 g of each antigen as a second vaccination and six weeks later developed a hard painful mass at the second injection site. The pain and the mass resolved over a few weeks with no biochemical evidence of muscle damage. The other with a severe delayed reaction developed pain and swelling in the thigh and around the knee two weeks after vaccination. There was marked discomfort on use. Symptoms resolved over two weeks with no biochemical evidence of muscle damage.

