The most common adverse event observed in trials using Montanide ISA720 is local reactogenicity (34). The acute reactions are characterized by of pain, swelling, induration, sterile abscess, and granuloma formation. These have been generally mild to moderate in 33 to 91% of volunteers. In the single Phase 2 trial in children in an endemic area the rate was 12% (26). The overall rate for mild and moderate acute local reactions is similar to that observed with licensed pediatric vaccines such as DT (standard pediatric dose) (55% mild/moderate local reactions) or dT (low dose vaccine) (52% mild/moderate reactions) in 6-year-old children. Severe local reactions occurred only with 5 vaccinees who received the vaccine via the intramuscular route for a cumulative rate of 1%. This proportion is not greater than that observed for some licensed vaccines (17% severe local reactions with DT and 11% severe local reactions with dT) (35). Severe local reactions were seen much more commonly in trials administering the vaccine subcutaneously. In these 2 trials (30) up to 44% of recipients of higher doses were not revaccinated due to local reactions. Acute local reactions were seen frequently with pain, swelling and/or induration most common. In the HIV vaccine study (33) sterile abscess and granuloma formation was seen in some volunteers, particularly those receiving the high antigen dose (2 mg), which was far in excess of that given in the malaria vaccine studies or that planned in this study. In most studies the vaccine was injected intramuscularly and when this route was used the majority of local reactions were mild to moderate with a cumulative rate of 1% for severe reactions. In contrast, severe local reactions were seen more commonly in the two studies in which the vaccine was administered subcutaneously (31, 32).

Delayed local reactions as seen in the Combination B studies (see Section 2.3.2) occurred in some volunteers in the majority of other trials with antigens formulated in Montanide® ISA720. Over all of the studies approximately 11% of volunteers developed these reactions, which were characterized by pain and swelling at the injection site occurring 10-28 days after vaccination. They resolved without sequelae usually in a few days but in some cases several weeks. There was a trend indicating that the rate and severity of these delayed reactions was increased with higher antigen doses and multiple injections.

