## 4.6 Subject Withdrawal Criteria

A volunteer will not be considered to have completed the trial if any of the circumstances outlined below apply. However, any volunteer who has received at least one dose of vaccine will be encouraged to remain in the safety evaluation for the duration of the study.

1. *Research terminated by sponsor, investigator, or regulatory body* – applies if the study is terminated by a sponsor, investigator, or regulatory body for any reason.
2. *Withdrawal of consent* – applies to a participant who withdraws consent to participate in the study for any reason.
3. *Noncompliant with protocol* – applies to a participant who does not comply with protocol-specific visits or evaluations, on a consistent basis, such that adequate follow-up is not possible and the participant’s safety would be compromised by continuing in the trial.
4. *Significant adverse event* - applies to a participant who is withdrawn from the study by the investigator due to an adverse event, serious or otherwise.
5. *Lost to follow-up* - applies to a participant who consistently does not return for protocol study visits, or who cannot be contacted or located.
6. If *new safety data* becomes available during the trial that impacts participant health.
7. *Pregnancy*. Should a female volunteer become pregnant during the course of the study, she will be withdrawn from the study and followed for the duration of the pregnancy. The outcome of the pregnancy will be documented.
8. If, in the judgment of the investigator, the subject has a condition that would interfere with safety or compliance with follow-up visits.
9. *Other* – is a category used when previous categories do not apply, and requires an explanation.

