1. Medical Investigator to perform medical history and physical examination including examination of injection site, emphasising examination of any acute complaints, to assess continued eligibility.
2. Record vital signs.
3. Collect Days 0-6 diary card and review completion. Refer any complaints to Medical Investigator for assessment.
4. Distribute Days 7-13 diary card.
5. Record adverse events and concomitant medications.

Study Day 14 +/- 2 (visit 4)

1. Medical Investigator to perform medical history and physical examination including examination of injection site, emphasising examination of any acute complaints and targetted history taking to elicit symptoms of muscle damage (myositis), as well as exercise history, emphasizing changes in pattern of regular exercise.
2. Record vital signs.
3. Collect Days 7-13 diary card and review completion. Refer any complaints to Medical Investigator for assessment.
4. Distribute Days 14-27 diary card.
5. Obtain approximately 14 mL of blood for haematology (FBC and differential), and biochemistry (creatinine, liver function tests, CPK).
6. Record adverse events and concomitant medications.

Study Day 21 +/- 3 (Phone call ONLY)

1. Phone call to inquire about diary card entries and injection site reactions since last visit.

Study Day 28 +/- 5 (1 month after FIRST vaccination, visit 5)

1. Study staff to perform targeted history and examine injection site, emphasising examination of any acute complaints, with review by the medical investigator if required.
2. Record vital signs.
3. Collect Days 14-27 diary card and review completion. Refer any complaints to Medical Investigator for assessment.
4. Obtain 55 ml of blood for collection of blood for humoral immunity studies by anti-MSP2 ELISA, and PBMC and serum for study of cell mediated immunity.
5. Record adverse events and concomitant medications.

Study Day 56 +/- 7 (2 months after FIRST vaccination, visit 6)

1. Medical Investigator to perform medical history and physical examination including examination of injection site, emphasising examination of any acute complaints, to assess continued eligibility.
2. Record vital signs.
3. Obtain approximately 9 mL of blood for haematology (FBC and differential), and biochemistry (creatinine, liver function tests).
4. Record adverse events and concomitant medications.

Study Day 84 +/- 7 (**SECOND vaccination, visit 7)**

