1. Medical Investigator to perform medical history and physical examination including examination of injection site, emphasising examination of any acute complaints and targetted history taking to elicit symptoms of muscle damage (myositis), as well as exercise history, emphasizing changes in pattern of regular exercise.

2. Record vital signs.

3. Obtain approximately 14 mL of blood for haematology (FBC and differential), and biochemistry (creatinine, liver function tests, CPK).

4. Collect Days 7-13 diary card and review completion. Refer any complaints to Medical Investigator for assessment.

5. Distribute Days 14-27 diary card.

6. Record adverse events and concomitant medications.

Study Day 105 +/- 3 (Phone call ONLY)
1. Phone call to inquire about diary card entries and injection site reactions since last visit.

Study Day 112 +/- 5 (28 days after SECOND vaccination, visit 11)

1. Study staff to perform targeted history and examine injection site, emphasising examination of any acute complaints, with review by the medical investigator if required.
2. Record vital signs.
3. Collect Days 14-27 diary card and review completion. Refer any complaints to Medical Investigator for assessment.
4. Obtain 55 ml of blood for collection of blood for humoral immunity studies by anti-MSP2 ELISA, GIA and IFA, and PBMC and serum for study of cell mediated immunity.
5. Record adverse events and concomitant medications.

Study Day 140 +/- 7 (56 days after SECOND vaccination, visit 12)

1. Medical Investigator to perform medical history and physical examination including examination of injection site, emphasising examination of any acute complaints, to assess continued eligibility.

2. Record vital signs.

3. Obtain approximately 9 mL of blood for haematology (FBC and differential), and biochemistry (creatinine, liver function tests).

4. Record adverse events and concomitant medications.

Study Day 168 +/- 7 (**THIRD VACCINATION, visit 13**)

1. Medical Investigator to perform medical history and physical examination, to assess continued
eligibility to enter treatment phase.

2. Obtain approximately 24 mL of blood for haematology, (FBC and differential), biochemistry (creatinine, liver function tests CPK), and humoral immunity studies by anti-MSP2 ELISA.

3. For females, obtain a urine sample for -hCG testing. Ensure that test is negative before vaccinating; a positive test will exclude the volunteer from the trial.

4. Record vital signs.

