5. Administer the vaccine in the alternate arm.

6. Observe for at least 30 minutes after vaccination to evaluate for immediate adverse reactions. Vital signs will be repeated prior to leaving the clinic.

7. Education by study staff during 30-minute post-immunisation wait period describing proper use of digital thermometers, injection-site reaction measurement tools, and patient diaries.  Study staff will also discuss signs and symptoms of potential AEs.

8. Distribute Days 0-6 diary card.

9. Record adverse events and concomitant medications

Study Day 169 (1 day after THIRD vaccination, Phone call ONLY)

1. Phone call to inquire about diary card entries and injection site reactions since last visit.
 
Study Day 171 (3 days after THIRD vaccination, visit 14)

1. Study staff to perform targeted history and examine injection site, emphasising examination of
any acute complaints, with review by the medical investigator if required.

2. Record vital signs.

3. Obtain approximately 9 mL of blood for haematology (FBC and differential), and biochemistry (creatinine, liver function tests).

4. Record adverse events and concomitant medications.

Study Day 175 +/- 1 (7 days after THIRD vaccination, visit 15)

Medical Investigator to perform medical history and physical examination including examination of injection site, emphasising examination of any acute complaints, to assess continued eligibility.

Record vital signs.

Collect Days 0-6 diary card and review completion. Refer any complaints to Medical Investigator for assessment.

Distribute Days 7-13 diary card.

Record adverse events and concomitant medications.

Study Day 182 +/- 2 (14 days after THIRD vaccination, visit 16)

1. Medical Investigator to perform medical history and physical examination including examination of injection site, emphasising examination of any acute complaints and targetted history taking to elicit symptoms of muscle damage (myositis), as well as exercise history, emphasizing changes in pattern of regular exercise.
2. Record vital signs.
3. Collect Days 7-13 diary card and review completion. Refer any complaints to Medical Investigator for assessment.
4. Distribute Days 14-27 diary card.
5. Obtain approximately 14 mL of blood for haematology (FBC and differential), and biochemistry (creatinine, liver function tests, CPK).
6. Record adverse events and concomitant medications.

Study Day 189 +/- 3 (Phone call ONLY)

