### 7.5.2 Process for Study Discontinuation

If the Principal Investigators, Sub-Investigators, Medical Monitor or sponsors have any further safety concerns, the SMC can be convened by the sponsors to review the safety data. The committee will provide verbal and hard copy written reports to the investigators and sponsors, who will then forward to the appropriate HREC/IRBs. Findings of a serious and immediate nature including any recommendations to modify or discontinue all or part of the study must be reported immediately in verbal and written form. Under circumstances where there are safety concerns that warrant no immunisation of a cohort, no further immunisations will be performed, and the Sponsors and all IRB/HRECs and Regulatory authorities will be promptly notified. All immunized participants will be followed for safety until resolution of their AEs or until at least 30 days after the last immunisation.

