Appendix 1 - MSP2 Schedule of Events

| **Procedures** | **WK** | **24** |  |  | **25** | **26** |  | **28** | **48** |
| --- | --- | --- | --- | --- | --- | --- | --- | --- | --- |
|  | **Day** | **168** | **1696** | **1716** | **1756** | **1826** | **1896** | **1966** | **336** |
| Clinical Evaluation |  | X |  | X | X | X |  | X | X |
| Distribute Diary Card |  | X**7** |  |  | X | X |  |  |  |
| Phone Call |  |  | X |  |  |  | X |  |  |
| Collect Diary Card |  |  |  |  | X | X |  | X |  |
| FBC & Diff, Biochem (9 mL)4 (14)5 |  | X5, 8 |  | X |  | X5 |  |  |  |
| Urine pregnancy test (females)3 |  | X7 |  |  |  |  |  |  |  |
| **VACCINATION** |  | **X7** |  |  |  |  |  |  |  |
| Anti-MSP2 antibody ELISA (10 mL) |  | X |  |  |  |  |  | X | X |
| Cell Mediated Immunity (45 ml=40 mL [PBMC] + 5 ml [serum]) |  |  |  |  |  |  |  | X**7** | X |
| Growth Inhibition Assay (GIA ) (from CMI plasma 2 mL for NIH assay) |  |  |  |  |  |  |  | X | X |
| Immunoflorescence Assay (IFA) with Ab (supernatent plasma off CMI whole blood) |  |  |  |  |  |  |  | X | X |
| Blood Volume (mL) |  | 19 |  | 9 |  | 14 |  | 55 | 55 |
| Cumulative Blood Volume (mL) | 285 | 304 |  | 313 |  | 327 |  | 382 | 442 |

**1 *Screening Consent,* 2*Particpation Consent,* 3 *Screening pregnancy (female only) = Serum Β-HCG (+10 mL blood) , 4Biochemistry to include: creatinine, AST and ALT,5 with CPK, 6 Visit Not required for Participant withdrawn from further Vaccination. 7 Procedure not required for Participant withdrawn from further Vaccination; 8 CPK not required if Participant withdrawn from further Vaccination***

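### Scheduled safety bloods and contact are sparsest after the third dose, and the minimum follow-up in Section 7.5.2 does not match Sections 4.6 and 6.4.1

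*Protocol*

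**What the plan says.** Section 6.4 and Appendix 1 give every dose the same early follow-up: clinic visits at 3, 7, 14 and 28 days, calls at 1 and 21 days, diary cards to day 27, and haematology with biochemistry at 3 and 14 days.

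Doses 1 and 2 then have a further visit with an examination and safety bloods, at "Study Day 56 +/- 7 (2 months after FIRST vaccination, visit 6") and "Study Day 140 +/- 7 (56 days after SECOND vaccination, visit 12"). Safety bloods are drawn again before the next injection, 84 days after the dose. Section 3.1 describes the 56-day visits as screening for the next dose.

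After dose 3 the last safety bloods are at "Study Day 182 +/- 2 (14 days after THIRD vaccination, visit 16"). In the row "FBC & Diff, Biochem (9 mL)4 (14)5" the cells for Days 196 and 336 are blank, although 55 mL is drawn for immunology on each of those days. Nothing is scheduled between them. At Day 336, Section 6.4 lists history and examination, vital signs and immunology blood. It is the only one of the 18 numbered visits without a step to record adverse events.

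Section 6.4.1 gives volunteers withdrawn from vaccination a modified schedule to Day 336. Section 4.6, whose list includes termination by the sponsor, looks to safety follow-up until the trial ends: "any volunteer who has received at least one dose of vaccine will be encouraged to remain in the safety evaluation for the duration of the" (the quotation stops one word short of the end of the sentence). Section 7.5.2, for a cohort stopped on safety grounds, says that participants will be "followed for safety until resolution of their AEs or until at least 30 days after the last immunisation".

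**The concern.** The primary objective is the safety and tolerability of three immunisations. Completers are the only volunteers who can inform the third, and their scheduled laboratory observation after the last dose is the shortest in the trial.

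Section 9.1.2 tabulates volunteers with at least one AE after each vaccination and plans longitudinal within-group comparisons with an exact McNemar test. Section 7.1.1 counts laboratory changes as AEs. If late laboratory changes are looked for after doses 1 and 2 but not after dose 3, a lower count after dose 3 partly reflects the schedule.

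The protocol's background also gives reasons to look beyond 28 days after a repeat injection. Section 2.3.2 describes a subject who "six weeks later developed a hard painful mass at the second injection site". Section 2.3.3 describes a delayed reaction that began 12 days after a third dose of another antigen in the same adjuvant, with swelling that took more than a month to resolve.

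**Working it through.** **Inputs.** Doses are at Days 0, 84 and 168. Safety bloods after a dose are at Days 3, 14, 56, 84, 87, 98, 140, 168, 171 and 182 (Section 6.4, Appendix 1). The Day 84 and Day 168 draws are pre-dose and are counted to the preceding dose. The last visit is Day 336.

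**The plan's own figure.** Section 3.2 gives 48 weeks of follow-up: 336 / 7 = 48.0. This reproduces.

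**Days since dose = study day minus dose day.**

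| | Dose 1 | Dose 2 | Dose 3 |
| --- | --- | --- | --- |
| Safety bloods, days after dose | 3, 14, 56, 84 | 3, 14, 56, 84 | 3, 14 |
| Last safety blood | 84 | 84 | 182 − 168 = 14 |
| Longest gap between scheduled contacts (nominal) | 56 − 28 = 28 | 140 − 112 = 28 | 336 − 196 = 140 |
| Calendar follow-up to next dose or study end | 84 | 84 | 336 − 168 = 168 |

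With the visit windows (Day 196 ± 5, Day 336 ± 14), the gap after dose 3 runs from 322 − 201 = 121 to 350 − 191 = 159 days.

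**Withdrawn volunteers (Section 6.4.1).** After dose 1 only, the last safety bloods are at Day 168, which is 168 − 0 = 168 days after the last dose. After dose 2 they are at Day 168, which is 168 − 84 = 84 days. Completers have 14 days. The withdrawn volunteers' draws omit CPK.

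**Where the cited reactions would fall.** Onset six weeks after dose 3 is Day 168 + 42 = 210. For the reaction at day 12, taking a month as 30 days, swelling would persist beyond 12 + 30 = 42 days, again Day 210. Both lie between Days 196 and 336. Section 7.2.1 requires such reactions to be measured at each visit until they resolve, but no visit is scheduled in that interval.

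**Opportunity to detect a laboratory AE arising after day 14.** Doses 1 and 2 have two scheduled draws each (56 and 84 days); dose 3 has none. Vaccine and control share one schedule, so this difference is across doses and not between arms.

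**Stopping text.** Sections 4.6 and 6.4.1 point to Day 336. Section 7.5.2 requires AE resolution or at least 30 days after the last immunisation, and does not say how the two limits combine. Its minimum is 42 − 30 = 12 days short of the six-week case.

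**The case against.** **The later bloods are eligibility checks.** Section 3.1 says so of the 56-day visits, the 84-day draws precede an injection, and no fourth dose exists. This explains how the asymmetry arose but does not justify it. Withdrawn volunteers, who receive nothing further, still have safety bloods 84 or 168 days after their last dose. That argument covers bloods only: the withdrawn volunteers' own schedule also has a long gap in contact, from Day 168 to Day 336.

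**Follow-up after dose 3 is not shortest.** This stands. A reader might infer a shortened safety period, but calendar follow-up is the longest of the three and ends with an examination of the injection site. Nor are volunteers out of reach: Section 6.4.2 allows unscheduled visits before Day 336, and Section 7.2.1 provides a clinician by telephone around the clock. What is missing is scheduled contact.

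**The background does not describe six-week reactions that increase with repeat injections.** This also stands. A reader might join the two statements, but the six-week mass is one subject, with no biochemical evidence of muscle damage. The trend that "the rate and severity of these delayed reactions was increased with higher antigen doses and multiple injections" concerns reactions at 10 to 28 days, a period covered almost identically after each dose. An event already open at Day 196 would be followed to resolution under Sections 7.2.1 and 7.3. The cited cases bear on the contact gap; they are not evidence of late laboratory toxicity.

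**The analysis harm is limited.** Partly right. Section 9.1.2 models laboratory values by treatment group and time, and the AE window may be set in a statistical analysis plan that is not shown. But laboratory AEs enter the per-vaccination tabulation, and no analysis window can supply bloods that were not drawn.

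**Thirty days is a floor.** Correct. It should not be read as a planned cut-off, and a minimum can coexist with encouragement to stay. The passages still leave it unclear which schedule applies to a stopped cohort.

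**Conclusion.** The point holds for laboratory follow-up and scheduled contact, and should be addressed. Scheduled safety bloods end 14 days after dose 3, against 84 days after doses 1 and 2, and the longest scheduled contact gap is 140 days against 28. Completers have later laboratory observation than neither group of withdrawn volunteers: 14 days, against 84 or 168.

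Comparisons of laboratory AEs across doses within a group are tilted toward dose 3 looking cleaner. The size depends on how often laboratory changes first appear after day 14, which the protocol does not give. For clinical AEs the direction is less certain: the 56-day examination is missing after dose 3, but its calendar window is twice as long (168 against 84 days). The documents give no ground for claiming bias between arms.

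This rests on counting pre-dose draws to the preceding dose and on reading the longitudinal comparisons in Section 9.1.2 as running across vaccinations. The mismatch between Section 7.5.2 and Sections 4.6 and 6.4.1 is a separate, smaller matter of wording.

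**What to change.** - Reconcile the safety-laboratory and contact schedule after dose 3 (Section 6.4, Appendix 1) with that after doses 1 and 2, with the modified schedules in Section 6.4.1, and with the reactions described in Sections 2.3.2 and 2.3.3; or state why less is adequate. The choice of time points is the sponsor's.
- Add adverse-event recording to the Day 336 visit in Section 6.4, and to the same visit in Section 6.4.1.
- Compare doses over a common post-dose window. On the present schedule, observation is matched to 14 days for laboratory AEs and to 28 days for clinical AEs.
- Reconcile Section 7.5.2 with Sections 4.6 and 6.4.1, and say how its two limits combine.

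The cost is small because 55 mL is already drawn at Days 196 and 336. For costing only: a safety sample is 9 mL, or 14 mL with CPK, so one at each visit would add 18 to 28 mL. The blood totals need correcting in any case: the last two entries in Appendix 1 give 382 + 55 = 437 mL, not the printed 442, and the approximate 450 mL in Section 6.0 should be checked against the revised sum. Any added telephone contact is one call for each of 30 volunteers. The rest is wording.
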